## **6 Adverse event observation and analysis**

All adverse events occurring during the study must be recorded and reported, and participants must be treated promptly and appropriately. Researchers will inform participants and ask them or their families to accurately report any changes in their condition post-treatment. Physicians should avoid leading questions. During efficacy observations, attention must be paid to adverse events. If incidents such as fainting, pain at the needle site, bleeding, hematoma, or infection occur during acupuncture, these will be recorded and appropriately handled until full recovery. Regardless of whether the adverse event is related to the treatment method, detailed records must be kept including the time of occurrence, symptoms, signs, severity, duration, lab test indicators, methods and results of treatment, course, follow-up times, and an analysis of the causes of adverse events.

## **7 Efficacy and safety evaluation**

### **7.1 Overall efficacy evaluation of participants**

(1) After completing all treatments, the effectiveness is assessed based on the "Traditional Chinese Medicine Syndrome Diagnosis and Treatment Standards" (2022 Edition) and improvements in patient observation indicators.

(2) After treatment, participants evaluate the effects of the acupuncture treatment.

### **7.2 Safety evaluation**

#### **7.2.1 Adverse events**

Record any adverse events (names, symptoms) that occur during different treat

ment regimens, including the time of occurrence, severity, measures taken, and outcomes, to assess their relevance to the treatment.

### 7.2.2 Safety assessment

Statistically compare adverse events that occur under different treatment regimens in this study and evaluate the safety of each regimen. Thoroughly document the time of occurrence, symptoms, severity, measures taken, and resolution of adverse events. In cases of adverse events, clinical physicians will decide whether to discontinue the trial based on the patient's condition, with severe cases being reported to the Medical Ethics Committee of the Second Affiliated Hospital of Yunnan University of Chinese Medicine within 24 hours, while also making the appropriate records.

## 8 Explanation of scale evaluations

### 8.1 Visual analogue scale

Use a 10cm VAS scale with a moving scale between 0 and 10 on the front and a number from 0 to 10 on the back, with 0 being no pain and 10 being the most painful.

Please state your pain level according to the following scale.

[figure not shown]

VAS scale (0-10 points)

0: no pain;1-3:light pain; 4-6:moderate pain; 7-10:severe and unbearable pain.

| Projects | Before treatment | Treatment |      |       |
|----------|------------------|-----------|------|-------|
|          | 0min             | 2min      | 5min | 10min |

|                |  |  |  |  |
|----------------|--|--|--|--|
| Pain VAS score |  |  |  |  |
|----------------|--|--|--|--|

## 8.2 Range of motion

In this study, lumbar range of motion will be measured using an angulometer as follows:

The patient stands upright with feet shoulder-width apart and muscles relaxed. For flexion and extension of the lumbar spine, the center of the goniometer is fixed at the lateral line of the body, transverse to the 5th lumbar spine. For lumbar lateral flexion, the center of the goniometer is aligned with the 5th lumbar spinous process. The stationary arm is positioned vertically to the ground, and the moving arm parallels the line from the 7th cervical to the 5th lumbar vertebra's spinous processes. During flexion and extension measurements, the patient bends forward or extends backward slowly, keeping the knees straight. In lateral flexion measurements, with hands on the occipital protuberance, the patient bends to each side, as depicted in Fig 3.

| lumbar ROM               |       | forward
flexion | backward
extension | left lateral
flexion | right lateral
flexion |
|--------------------------|-------|--------------------|-----------------------|-------------------------|--------------------------|
| Normal range
(degree) |       | 0°-90°             | 0°-30°                | 0°-30°                  | 0°-30°                   |
| Before
treatment      | 0min  |                    |                       |                         |                          |
| Treatment                | 2min  |                    |                       |                         |                          |
|                          | 5min  |                    |                       |                         |                          |
|                          | 10min |                    |                       |                         |                          |

[figure not shown]

**Fig 3 Lumbar motion measurement**

## **9 Quality control and assurance**

### **9.1 Analysis of study influencing factors**

#### **9.1.1 Analysis**

(1) Selection Bias: To avoid selection bias, the most effective measure is the use of a randomized control design, especially the random assignment of subjects into groups to ensure balanced and comparable groups. This prevents researchers from arbitrarily deciding group assignments or treatments based on subjective desires, thus avoiding biased outcomes.

(2) Measurement Bias: When measuring outcomes between AA and SAA groups, especially when it's known which group is which, measurement observations are likely to differ due to subjective reasons, leading to judgment biases, particularly in non-blinded observations.

(3) Confounding Bias: Confounding bias mainly appears during the result analysis phase, where two factors may be intertwined or affect each other, possibly attributing

the cause of a result incorrectly due to other co-existing factors (confounders) that could produce the same outcome, leading to exaggerated or minimized conclusions.

### **9.1.2 Control**

(1) Choice of Study Design: This study uses a randomized control design, which is the most effective way to avoid selection bias.

(2) Strict Selection of Subjects: Strict inclusion criteria are one of the important methods to control bias. Establishing clear inclusion and exclusion criteria restricts study subjects to a specific range, reducing differences and facilitating objective conclusions about observed factors.

(3) Blinded Measurement and Judgment: Blinding is the most effective way to avoid measurement biases by researchers and subjects. If the researcher knows which treatment a participant is receiving, they might unconsciously favor reporting improvements in the treatment group. Although researchers may be honest, they tend to hope for favorable outcomes, thus the best way to avoid this bias is through blinded measurements and judgments. Although acupuncturists will be aware of the treatment allocations, they will not participate in the subsequent outcome assessment or data analysis. Blinded statistical analysis during the data summarization stage to ensure the reliability of the study results.

## **9.2 Research training**

To ensure the smooth conduct of the study, a specialized clinical training session will be held before the start of the study. All researchers will receive uniform training on the implementation plan and detailed operational training to familiarize and master

the research process and specific implementation rules, enhancing internal consistency among researchers and between observers, and ensuring the reliability of research conclusions.

### **9.3 Measures to improve participant compliance**

To achieve better compliance, ensuring that the number of cases analyzed at the end is no less than 80% of those entering the study, the following measures will be used: adhere to the principle of voluntariness, sign informed consent forms with participants and their families; improve and maintain good compliance through medical quality, clinic environment, and medical costs, encouraging participants to adhere to the treatment during the study; establish good doctor-patient relationships, explain the condition, treatment purposes and necessity in detail, and obtain consent and cooperation from participants. Communicate with patients before starting treatment, observe the efficacy after one treatment session, and if the subsequent relief is not significant, offer two additional acupuncture treatments free of charge. At the end of the treatment, review and perfect the relevant records together with the participants.

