**Fig 2. Auricular needle and Sham auricular needle**

### **4.3 Procedures**

(1) Auricular acupuncture group: Participants will be in a seated position. The acupuncturist will sterilize the skin of the healthy side AH9 with a 70% alcohol swab. Subsequently, a disposable auricular needle will be pierced vertically into the healthy side AH9. After needle insertion, moderate pressure will be applied to elicit the "de qi" sensation. Upon achieving "de qi", participants will be asked to stand. The acupuncturist will stand behind the participant and support the participant's waist. Then, the participant will be guided through moderate exercises, including forward bending, backward stretching, lateral bending, and rotation, all performed within the limits of their pain tolerance. The range and speed of these movements will gradually increase as the pain decreases.

(2) Sham auricular acupuncture group: This group will receive treatment with a placebo needle of the same shape which lacks a needle body and does not penetrate the skin but is merely taped at the acupoint. The treatment operation is the same as the AA group.

Participants in both groups will receive a single treatment session, with a 10-minute auricular needle retention time.

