#### **4.4 Remedial pain management**

If patients experience intolerable lower back pain that does not improve post-treatment, they will take the non-prescription NSAID pain reliever ibuprofen. The dosage, time of administration, and the duration until pain relief are recorded.

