#### **4.5 Observation period**

Baseline assessments will be performed before enrollment, and pain intensity and ROM evaluations will be conducted 2, 5, and 10 minutes post-treatment.

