## **5.4 Measurement indicators**

### **5.4.1 Primary outcome**

The primary outcome will be the change in pain intensity from baseline to 10 minutes after treatment as measured using VAS scores.

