### **5.4.2 Secondary outcomes**

(1) Changes in pain intensity at 2 and 5 minutes after treatment will also be measured using VAS scores.

(2) Lumbar range of motion (ROM) will be assessed at baseline, 2, 5, and 10 minutes during treatment. Participants will be instructed to stand with their feet slightly apart, shoulder width apart, and their body relaxed. Measurements will be taken for forward flexion, backward extension, right lateral flexion, and left lateral flexion in order.

(3) Patient expectations of treatment outcomes will be assessed at baseline using the efficacy expectations scale.

(4) The success of the blinding will be assessed at the end of treatment using a blinded questionnaire.

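### Section 4.3 fixes one treatment session, but section 9.3 offers two more when relief is poor, and nothing keeps those sessions out of the overall efficacy rating, the blinding check or the adverse-event comparison

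*Protocol*

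**What the plan says.** Protocol section 4.3 states: "Participants in both groups will receive a single treatment session, with a 10-minute auricular needle retention time". Section 4.5 ends the efficacy schedule at 10 minutes: "pain intensity and ROM evaluations will be conducted 2, 5, and 10 minutes post-treatment". The primary outcome in 5.4.1 is the "change in pain intensity from baseline to 10 minutes after treatment as measured using VAS scores".

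Section 9.3 lists measures to improve compliance. Staff are to talk with patients before treatment, "observe the efficacy after one treatment session", and then, "if the subsequent relief is not significant, offer two additional acupuncture treatments free of charge". The sentence that follows sets the joint review of the records at the end of treatment.

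Three other parts of the protocol are timed by the end of treatment or by the study as a whole:

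- Section 7.1, overall efficacy: "After completing all treatments, the effectiveness is assessed based on" a published standard and the improvement in the observed indicators.
- Section 5.4.2, item 4: "The success of the blinding will be assessed at the end of treatment using a blinded questionnaire".
- Sections 7.2.2 and 11.1.6: adverse events are compared between regimens and counted over the study, including by relatedness to acupuncture.

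Section 4.4 covers intolerable pain that does not improve after treatment. There, "they will take the non-prescription NSAID pain reliever ibuprofen", and no further acupuncture is mentioned.

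**The concern.** The two sections disagree on how many sessions a participant may have. A site following 4.3 gives one, and a site following 9.3 may give three. Section 9.3 leaves open the trigger, the type of needle, the timing, and whether the sessions are trial treatment or care after the trial. It is also not linked to section 4.4, which gives a different response to pain that persists.

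The extra sessions depend on response, so they would not be spread evenly over the arms. Any assessment that can include them may compare participants with different amounts of treatment, with the imbalance driven by the outcome itself. If the extra needles were real, which the text neither says nor rules out, sham participants could bring real-needle adverse events into the sham column. They could also form an opinion about their first needle before answering the blinding questionnaire.

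**Working it through.** **Order of events.** Section 9.3 runs: communicate, observe efficacy after one session, then make the offer. Sections 4.5, 8.1 and 8.2 schedule VAS and ROM at 0, 2, 5 and 10 minutes and nothing later. The extra sessions therefore follow every scheduled VAS and ROM reading, and the primary outcome and the listed pain and ROM outcomes cannot be changed by the sessions themselves.

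**Assessments without that protection.**

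| Assessment | Timing as written | Can it include extra sessions? |
|---|---|---|
| VAS and ROM at 2, 5, 10 minutes | Fixed minutes of the first session | No |
| Overall efficacy (7.1) | After all treatments, in the plural | Yes |
| Blinding questionnaire (5.4.2) | End of treatment | Yes if 9.3 governs, no if 4.3 governs |
| Adverse events (7.2.2, 11.1.6) | During the study | Yes |
| Compliance (11.1.5, item 3) | Has a category above 100% | Possibly; the category is hard to explain with one session |

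**Who would qualify.** The point disputes no figure in the plan, but it borrows the inputs of section 2.2: a VAS fall of 4.6 (SD 1.0) with real needles and 2.7 (SD 1.0) with sham. Those inputs reproduce the stated sample size: (1.960 + 1.282)² × 1.0² × 2 / (4.6 − 2.7 − 1.3)² = 58.4 per group, stated as 58. Then 58 / 0.92 = 63.04, so 64 per group and 128 in total.

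Section 9.3 sets no threshold, so take an assumed one: the participant qualifies if the VAS fall is below c, with normally distributed falls. The share qualifying is Φ((c − mean)/1.0), and the count is 64 times that share.

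| Assumed c | Sham | Real needles |
|---|---|---|
| 2 points | Φ(−0.7) = 24.2%, about 15 | Φ(−2.6) = 0.5%, about 0.3 |
| 3 points | Φ(0.3) = 61.8%, about 40 | Φ(−1.6) = 5.5%, about 4 |

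At either threshold the extra sessions fall mainly in the sham arm. These are counts of people eligible for the offer. They are not estimates of bias.

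**Could knowledge of the offer shift the 10-minute VAS?** Someone already below the threshold gains nothing by reporting less relief. An incentive would act on people just above it. Suppose, purely as an assumption, that everyone within 0.5 point above c reports 0.5 point less relief. The change in the arm difference is 0.5 × (sham share − real-needle share).

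| Assumed c | Sham share | Real-needle share | Shift in difference |
|---|---|---|---|
| 2 | 17.9% | 1.3% | +0.08 |
| 3 | 17.0% | 8.1% | +0.04 |
| 4 | 6.1% | 18.6% | −0.06 |

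The sign changes with a threshold that the protocol does not give.

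**The case against.** The strongest reply is that the damage is narrow. The primary outcome and the timed secondary outcomes are complete before any offer. The overall rating in 7.1 is not a listed primary or secondary outcome. Under 4.3 the end of treatment is the end of the single session, which would place the blinding questionnaire correctly. Sections 6 and 11.1.6 already require the time of each adverse event, so later events can be separated afterwards. The first two of these points stand in full. The third holds only if 4.3 prevails over 9.3, which is the matter in dispute. The fourth shows that the data for a separate table would exist, but no such table is required.

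Two stronger readings are tempting:

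- **Sham participants cross over to real needles.** A reader might infer this, but 9.3 does not name the type of needle. Crossover is not excluded, and it is not provided for either.
- **The offer rewards low reported relief and so inflates the treatment effect.** This needs participants to know of the offer before the 10-minute rating. Section 9.3 mentions communication before treatment without saying what is communicated, and it does not tie the offer to the VAS score. Trial treatment is in any case free to all participants (12.3, item 6). Even if disclosure came early, the working shows that the direction depends on an unstated threshold.

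**Conclusion.** The contradiction between 4.3 and 9.3 is certain and rests on the text alone. As written, response-dependent extra sessions can enter the overall efficacy rating, the blinding questionnaire and the adverse-event comparison. On the protocol's own predicted changes they would fall mostly in the sham arm: about 15 against 0.3 participants of 64 at an assumed 2-point trigger, and about 40 against 4 at an assumed 3-point trigger. Those counts assume normal distributions and a trigger defined on the VAS fall.

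The 2-, 5- and 10-minute VAS and ROM are not altered by the sessions. Early knowledge of the offer could influence self-reported pain, but neither the direction nor the size follows from the protocol, so no magnitude of bias is claimed. This is a point that should be fixed. It does not threaten the primary analysis.

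**What to change.** 1. Reconcile sections 4.3 and 9.3 on the number of sessions, and state whether any later session is part of the trial. Make the relation to section 4.4 clear in the same edit. Which clinical rule applies is for the sponsor to decide.
2. State in 5.4 and 7.1 that the efficacy, overall-effect and blinding assessments are completed at the end of the first session and use data to that point only.
3. Tabulate adverse events that start after any further session separately, by treatment actually received. The main between-arm comparison then covers the randomised session.

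The cost is a few sentences in 4.3, 9.3, 5.4 and 7.1 and one extra adverse-event table. The sample size and the primary analysis do not change.

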### **9.4 Quality control and assurance system**

The project leader will supervise and inspect the entire study process, ensuring all study data records, reports, and case report form entries are true, accurate, and complete, and consistent with the original data.

## **10 Data management**

Researchers are responsible for data management of the project, with supervision by

the project leader.

## **10.1 Definition of original data**

- (1) All original records entered in the case report forms;
- (2) All original data from laboratory tests and other examination reports.

## **10.2 Data recording**

Researchers must fill in clinical research records promptly, accurately, completely, in a standardized manner, and truthfully.

- (1) All cases must be documented and CRFs filled in completely as per the study protocol, with no fields left blank (use a diagonal line for any spaces without records);
- (2) Medical records and CRFs, as original records, can only be corrected by striking through, annotating the revised data with reasons, and must be signed and dated by the clinician and researcher involved in the clinical study; no erasing or covering of original records is allowed;
- (3) Data significantly above or beyond clinically acceptable ranges must be verified, with necessary explanations provided by the attending clinician;
- (4) After the treatment observation of each participant is complete, researchers must submit the case report forms and medical records to the principal investigator for review and signature within one week.

## **10.3 Data verification**

- (1) The principal investigator must periodically verify that researchers are following the study protocol, checking participants' informed consent and screening inclusion;
- (2) Confirm all case report forms are filled in promptly and correctly and consistent

with original data; all errors or omissions are corrected or noted, signed and dated by the researchers; any changes in treatment alterations, concomitant medications, complications, or missed examinations must be confirmed and recorded;

(3) Ensure that reasons for participant withdrawals are noted in the case report forms; all adverse events, especially serious adverse events, must be reported and recorded within the specified time.

## **11 Statistical analysis**

Clinical data part will be handled by Yunnan University of Traditional Chinese Medicine, using SPSS for statistical analysis.

### **11.1 Statistical analysis content and methods**

#### **11.1.1 Statistical analysis sets**

##### **11.1.1.1 Efficacy evaluation data set**

(1) Full Analysis Set (FAS): Includes all randomized participants. For cases not observed throughout the entire treatment process, the last observed outcome (last observation carry-forward: LOCF) is carried forward to the point of data missing. The number of participants evaluated for efficacy at the endpoint is consistent with the number at the start of the study. Comprehensive efficacy analysis is conducted using the Per Protocol Set (PPS) and the Full Analysis Set.

(2) Per Protocol Set (PPS): Includes participants who complied with the study treatment protocol, primarily those who can be measured for key indicators and have no major violations of the study protocol. Analyses of demographic and other baseline characteristics and other efficacy indicators are conducted using the PPS.

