#### **11.1.4 Efficacy evaluation**

All efficacy evaluation data will be summarized separately according to the FAS and PPS sets, with the FAS set as the primary analysis method.

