#### **11.1.5 Statistical analysis methods**

This study utilizes SPSS 28.0 for the analysis of clinical data. Continuous variables with normal distribution will be expressed as mean  $\pm$  SD and continuous variables with non-normal distribution will be reported as median and interquartile range (IQR).

For analyzing demographic data, continuous variables will be analyzed using the independent samples t-test or the Wilcoxon rank sum test depending on whether or not they conform to a normal distribution. Categorical variables will be analyzed using  $\chi^2$  test or Fisher's exact test. All significant demographic differences will be included as covariates in subsequent efficacy analyzes. The primary outcome indicator will be analyzed using analysis of covariance with baseline pain levels as a

covariate and group as a factor. The secondary outcomes, including changes in pain intensity at other time points (2, 5 minutes) and ROM at different time points, will be analyzed using repeated measures ANOVA or Mann-Whitney U test, depending on the data's distribution. Additionally, correlations between pain VAS scores and efficacy expectation scores will be explored using Spearman's or Pearson's correlation analysis. We will follow the intention-to-treat (ITT) principle and analyze all participants who receive treatment. Missing data of withdrawn participants will be processed using chained-equation multiple imputation.

(1) Case Distribution: Size of different data sets in each group, distribution of cases across centers, detailed list of dropouts, discontinuations, and reasons.

(2) Comparability Analysis: Compare demographic data and other baseline values to assess comparability between groups.

(3) Compliance Analysis: Compare whether patients in each group followed the design protocol. Compliance is evaluated based on the records in the participant's CRF form, calculating percentages for <80%, 80%–100%, and >100% compliance.

(4) Factors Affecting Efficacy Analysis: If there are significant differences between groups before the study or factors significantly affecting efficacy, these factors should be considered as covariates in the group comparisons, requiring covariance analysis or logistic regression, and a detailed list of concomitant medication use.

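### The primary 10-minute VAS change has two incompatible missing-data rules (LOCF and multiple imputation) and two populations, and the protocol ranks neither

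*Protocol*

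**What the plan says.** The primary outcome (protocol section 5.4.1) is "the change in pain intensity from baseline to 10 minutes after treatment as measured using VAS scores". Section 4.5 states that "pain intensity and ROM evaluations will be conducted 2, 5, and 10 minutes post-treatment".

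Two sets of instructions then apply to a participant whose 10-minute value is missing.

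- **Sections 11.1.1.1 and 11.1.4.** The FAS is defined by the words "Includes all randomized participants". For cases not followed through the whole treatment, "the last observed outcome (last observation carry-forward: LOCF) is carried forward to the point of data missing". Efficacy is summarized on the FAS and the per-protocol set, "with the FAS set as the primary analysis method".
- **Section 11.1.5.** "The primary outcome indicator will be analyzed using analysis of covariance with baseline pain levels as a" covariate and group as a factor. The same paragraph invokes intention to treat but says the trial will "analyze all participants who receive treatment", and then: "Missing data of withdrawn participants will be processed using chained-equation multiple imputation".

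Two other places bear on who is analysed. Section 3.1.5(4) puts every excluded or dropped case into the intention-to-treat analysis. Section 3.1.6(4) speaks of including in the efficacy analysis those who have passed half of the treatment duration.

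**The concern.** LOCF and multiple imputation are different estimators for the same missing number, and they rest on different assumptions. Neither is called primary or sensitivity, and neither is tied to an endpoint or a reason for missingness, so they cannot be read as complementary. An analysis plan that follows one departs from the other. Which result counts as primary is therefore not fixed by the protocol.

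LOCF also fits this outcome poorly. It assumes that pain stops changing at the last reading, whereas section 2.2 plans on mean falls of 4.6 (AA) and 2.7 (SAA) by 10 minutes. A carried baseline records no change at all, and an earlier post-baseline reading probably records only part of it. The single filled-in value then enters the ANCOVA as if it had been measured, so imputation uncertainty is ignored.

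**Working it through.** **1. The texts side by side**

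| | Sections 11.1.1.1 and 11.1.4 | Section 11.1.5 |
|---|---|---|
| Population | all randomized | all who receive treatment |
| Missing values | LOCF | chained-equation multiple imputation |
| Status | FAS named primary | stated beside the primary ANCOVA |

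A participant who withdraws before the 10-minute reading is covered by both columns. One randomized but never treated is in the first population and outside the second. This step needs no arithmetic.

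**2. The plan's own sample size**

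Inputs from section 2.2: changes 4.6 and 2.7, SD 1.0, one-sided alpha 0.025, beta 0.1, margin 1.3, 1:1 allocation, 8% dropout.

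n = (1.960 + 1.282)² × 1² × 2 / (4.6 − 2.7 − 1.3)² = 58.37 per arm.

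The plan states 58, where power is 89.8%; at 59 it is 90.3%. 58 / 0.92 = 63.04, so 64 per arm and 128 in total, as stated. The missing-data rule does not change N.

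**3. What LOCF does to the difference**

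Assumptions, because the documents give no 2- or 5-minute values and no dropout by arm:

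- 8% of 64 is about 5 lost per arm, and 8% of 128 is about 10 in all.
- Dropouts would have responded like completers.
- A share f of the final change has been reached at the last reading.

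Mean change in an arm with k of 64 lost = μ × [1 − (k/64)(1 − f)].

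- 5 per arm, f = 0: 4.6 × 59/64 − 2.7 × 59/64 = 4.241 − 2.489 = **1.75** (true value 1.90).
- 5 per arm, f = 0.4: 1.90 × (1 − 0.078 × 0.6) = **1.81**.
- 5 per arm, f = 0.7: 1.90 × (1 − 0.078 × 0.3) = **1.86**.
- 5 in AA only, f = 0: 4.241 − 2.7 = **1.54**.
- 5 in SAA only, f = 0: 4.6 − 2.489 = **2.11**.
- All 10 in AA, f = 0: 4.6 × 54/64 − 2.7 = **1.18**.
- All 10 in SAA, f = 0: 4.6 − 2.7 × 54/64 = **2.32**.

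**4. What it does to power**

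Carrying baseline shrinks the difference and also widens the spread, because zeros are mixed with full responses. With an 8% chance of loss (d) in each arm and f = 0, the variance in an arm is (1 − d) + d(1 − d)μ²:

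- AA: 0.92 + 0.0736 × 21.16 = 2.477
- SAA: 0.92 + 0.0736 × 7.29 = 1.457
- SE = √(3.934/64) = 0.248

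Power against 1.3 is then Φ[(1.748 − 1.3)/0.248 − 1.96], about 44%. Simulation with exactly 5 lost per arm (40,000 trials, Welch 95% lower limit) gives:

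| Scenario | Difference | Power against 1.3 | Power against 0 |
|---|---|---|---|
| 59 complete per arm | 1.90 | about 90% | near 100% |
| LOCF, f = 0 | 1.75 | about 41% | near 100% |
| LOCF, f = 0.4 | 1.81 | about 74% | near 100% |
| LOCF, f = 0.7 | 1.86 | about 87% | near 100% |

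With 5 lost in AA only and baseline carried, power against 1.3 is about 10%; with 5 lost in SAA only it is about 99%. Against zero it is 99% or more in every scenario. Multiple imputation with data missing at random would leave the difference at 1.90 and power against 1.3 at about 90%.

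**The case against.** **The power loss may not be real.** A reader might infer that LOCF halves the trial's power. The documents do not support that. The 1.3 margin appears only in the sizing formula of section 2.2; section 11.1.5 names no margin for the ANCOVA, and against zero almost nothing is lost. The 41% figure also needs every dropout to leave before the 2-minute reading. In a single session with 10 minutes of needle retention, few 10-minute values may be missing, and section 3.1.5(1) tells staff to record the last data and complete what assessments they can. This stands: the figure is a conditional extreme.

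**LOCF need not be the more biased rule.** Sections 3.1.5(2) and 3.1.6(1) foresee withdrawal for ineffective treatment or increased pain. For such patients a carried low response may lie nearer the truth than imputation under missing at random. This stands too. The stronger reading, that LOCF biases this trial in a known direction, goes beyond the text.

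**Blinded analysts cannot pick the favourable result.** Section 2.4 blinds the statistical analysts to group. That limits directional choice, but it does not say which rule is primary.

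**A statistical analysis plan may settle it.** That would answer a missing detail. Here the protocol fixes two rules, so any plan must contradict one of them.

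**Conclusion.** The conflict is literal and holds with high confidence: two unranked missing-data rules and two populations for the primary endpoint. LOCF is also at odds with the plan's own expectation of a rapid fall in pain.

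The size of the effect has low confidence. With equal loss of 5 per arm and dropouts otherwise like completers, the difference shrinks by 0.04 to 0.15 of 1.90 for f between 0.7 and 0. With baseline carried and all loss in one arm, it ranges from 1.18 (10 lost in AA) to 2.32 (10 lost in SAA). Timing, reasons and arm split of dropout are all assumed, so the bias could run either way or be negligible. The power figures apply only if the sizing margin is also the test margin, which the protocol does not state.

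This should be fixed before unblinding because the primary analysis is not uniquely specified. A large bias has not been shown.

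**What to change.** - Delete the LOCF sentence from section 11.1.1.1 and define the FAS by membership only.
- In section 11.1.5, name multiple imputation as the single primary rule for the 10-minute VAS change, run by arm with baseline, 2-minute and 5-minute VAS in the imputation model.
- Keep LOCF, if at all, as a labelled sensitivity analysis.
- Align the population wording in sections 11.1.5 and 3.1.6(4) with the all-randomized FAS. Otherwise the imputation still has no single defined population.

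Naming either rule as primary would remove the contradiction. Multiple imputation is preferred because it is already planned, does not force a flat course, and carries imputation uncertainty into the standard error. The cost is wording only: the predictors are already collected and N stays at 128.
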